## Abstract

**Background:**

Emotion regulation is an ability related to psychological well-being; when dysregulated, individuals may have psychiatric symptoms and maladapted physiological responses. Virtual reality–assisted cognitive behavioral therapy (VR-CBT) is an effective psychotherapy to target and strengthen emotion regulation; however, it currently lacks cultural sensitivity and can be improved by adapting it to the cultural context of service users. During previous participatory research, we co-designed a culturally adapted cognitive behavioral therapy (CBT) manual and 2 virtual reality (VR) environments to function as a complement to therapy (VR-CBT) for Inuit who would like to access psychotherapy. Emotion regulation skill building will occur in virtual environments that have interactive components such as heart rate biofeedback.

**Objective:**

We describe a protocol for a proof-of-concept 2-arm randomized controlled trial (RCT) with Inuit (n=40) in Québec. The primary aims of this research are to investigate the feasibility, benefits, and challenges of the culturally adapted VR-CBT intervention versus an established VR self-management that is available commercially. We will also investigate self-rated mental well-being and objective psychophysiological measures. Finally, we will use proof-of-concept data to identify suitable primary outcome measures, conduct power calculations in a larger trial for efficacy, and collect information about preferences for on-site or at-home treatment.

**Methods:**

Trial participants will be randomly assigned to an active condition or active control condition in a 1:1 ratio. Inuit aged 14 to 60 years will receive a culturally adapted and therapist-guided VR-CBT with biofeedback or a VR relaxation program with nonpersonalized guided components over a 10-week period. We will collect pre- and posttreatment measures of emotion regulation and biweekly assessments over the treatment and at 3-month follow-up. The primary outcome will be measured by the Difficulties in Emotion Regulation Scale (DERS-16) and a novel psychophysiological reactivity paradigm. Secondary measures include psychological symptoms and well-being via rating scales (eg, anxiety or depressive symptoms).

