### Measures

#### Primary Outcome Measures

### DERS-16 Scores

The DERS-16 is a short, valid measure of emotion regulation [29,44]. Participants rate their ability to accept and be aware of their emotions, direct themselves toward their goals, control their impulses, access regulation strategies, and have emotional clarity [45]. The DERS’s psychometric properties are favorable, having moderate to very strong internal consistency (α=.69-.97) and strong retest reliability (*r*=0.88; ρI=0.85) [29, 46-49]. Correlating with anxiety, depression, stress, borderline traits, and more, the DERS-16 has good construct validity [29,47,50]. Although consistent across demographics and culturally adapted for some groups, the scale is not yet adapted for any Indigenous groups [48,51]. The full DERS is translated into French and validated [52]. Although there are no formal cutoff scores for the DERS, the English scale achieves moderate diagnostic accuracy (area under the curve [AUC]) among emotional disorders and nonsuicidal self-injury populations [53-55], and it is sensitive to changes following treatment [56-60].

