### Visual Analog Scales: Anxiety, Emotional Arousal, Emotional Valence

Participants will respond to the Visual Analog Scale (VAS)-Anxiety (VAS-A), Visual Analog Scale-Emotional Arousal (VAS-EA), and Visual Analog Scale-Emotional Valence (VAS-EV) during reactivity testing. These items have favorable properties, including construct validity and sensitivity [37-40].

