### Objective Measures

The participants will undergo a psychophysiological reactivity testing paradigm. This will be repeated after the end of the VR intervention for those who completed a minimum of 7 and a maximum of 10 sessions of therapy as soon as possible after the final session. We will collect and measure several metrics, including heart rate, blood volume pulse, skin conductance, blood pressure, and accelerometer data. Participants first respond to baseline subjective arousal, emotional arousal, and VAS-EV. We then begin collecting psychophysiological data with a portable finger sensor, covered with a piece of cloth for light sensitivity, by attaching it to the participant’s nondominant index finger. They fill out a survey, including several symptom scales as described during this approximately 15-minute period, and have their blood pressure taken with an ambulatory blood pressure machine. We also record a no-task seated baseline recording of sensor data for 3 minutes. Then, participants will familiarize themselves with VR in a forest walk environment with no tasks other than to walk and explore (5.5 minutes), with minimal interaction with the research team. In the next segment, participants walk a VR plank exposing them to the heights below for 5.5 minutes (instructed to walk back and forth, with no interaction). If the exercise is too challenging (eg, participant distress at a tolerable level), participants remain in the environment without walking for 2 minutes or withdraw completely (eg, intolerable distress) from the exercise. Finally, participants re-enter the same VR environment, this time with a floor rather than a plank beneath them and walk (3 minutes). The last segment is a 10-minute seated rest period. After each segment, participants report using the same visual analog scales.

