### Data Analysis

#### Analyses for Rating Scales

Expecting nonnormally distributed data in a small human sample, we will conduct nonparametric tests and generate descriptive and comparative statistics to detect between-group differences for the 2 conditions, VR-CBT (A) and Active Control VR program (B), using R Statistical and Computing Software (R Core Team). We will use generalized mixed linear models to compare the 2 conditions using scores on DERS-16 across several time points (pre- and posttreatment as well as biweekly and bimonthly time points). In addition, we will describe changes in mood, anxiety, and trauma symptoms for the 2 conditions (pre- and posttreatment, as well as biweekly and bimonthly time points). The data collection for time points varies based on the administration instructions for each scale (weekly, biweekly, monthly, etc). Cohen *d* or nonparametric tests will calculate the effect size between the 2 conditions.

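### The primary outcome is two unranked components covering up to nine measures, with no primary time point and no deciding analysis for DERS-16

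*Protocol article*

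**What the plan says.** - **Primary outcome (Abstract, Methods).** "The primary outcome will be measured by the Difficulties in Emotion Regulation Scale (DERS-16) and a novel psychophysiological reactivity paradigm". The two parts are joined by 'and'. Neither is put first and no time point is attached.
- **Measures listed between the primary and secondary headings.** DERS-16 comes first: "The DERS-16 is a short, valid measure of emotion regulation". Next come three scales: "Participants will respond to the Visual Analog Scale (VAS)-Anxiety (VAS-A), Visual Analog Scale-Emotional Arousal (VAS-EA), and Visual Analog Scale-Emotional Valence (VAS-EV". Objective Measures then adds: "We will collect and measure several metrics, including heart rate, blood volume pulse, skin conductance, blood pressure, and accelerometer data". The visual analog scales recur within each reactivity session: "After each segment, participants report using the same visual analog scales".
- **Analysis (Analyses for Rating Scales).** "we will conduct nonparametric tests and generate descriptive and comparative statistics to detect between-group differences for the 2 conditions". The same section then compares the two conditions on DERS-16 with generalized mixed linear models, "across several time points (pre- and posttreatment as well as biweekly and bimonthly time points". Effect size is to come from Cohen d or nonparametric tests. Adjustment for baseline is not mentioned.
- **Sample Size.** 20 per group, effect size similar to g = 0.78 or 0.90, df = 38, P = .05, stated power 0.97. This describes one two-group comparison, and the outcome is not named.
- **Purpose.** The VR-CBT subsection on co-design says efficacy will be evaluated. The Abstract (Objective) and Research Aims put feasibility first, and the Abstract wants the data to identify suitable primary outcomes and to support power calculations for a larger trial.

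**The concern.** A primary outcome should point to one result. Here a reader cannot tell before the data are seen whether the trial's main efficacy estimate will be a DERS-16 difference, a heart-rate or skin-conductance response, or an anxiety rating after one of the reactivity segments. Nor can the reader tell at which visit it is taken or, for DERS-16, by which method.

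Two things are at stake. First, the error rate implied by one test at .05 no longer holds if several measures are tested at that level. Second, and more important for a proof-of-concept trial, the estimate carried into the larger trial's power calculation could be chosen because it looks best. With 20 per group such a choice favours effects inflated by chance, and the next trial would then be too small.

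**Working it through.** **1. The plan's own figure.** Two groups of 20, df = 38, two-sided .05. The noncentrality is d × √(20×20/40) = d × 3.162.

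- d = 0.78: noncentrality 2.47, power 0.67 (one-sided 0.78).
- d = 0.90: noncentrality 2.85, power 0.79 (one-sided 0.87).

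The stated 0.97 is not reproduced; a two-sided test would need d of about 1.25. That is a separate matter and this point does not rest on it. What matters here is that the statement covers one comparison, with no alpha shared across outcomes.

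**2. Count of measures.** DERS-16 (1) + visual analog scales (3) + named signals (5) = 9. The signal list is introduced by 'including', so it is open. If accelerometry serves only to control motion artefact, the count is 8.

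**3. Chance of at least one false positive, each measure tested at .05.** For k independent measures this is 1 − 0.95^k. For correlated measures, 200,000 simulated sets of two-sided z tests with a common correlation were used. The documents give no correlations, so these are assumed.

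| Measures | Correlation | Chance of at least one |
|---|---|---|
| 2 components | 0 | 1 − 0.95² = 9.8% |
| 8 | 0 | 1 − 0.95⁸ = 33.7% |
| 9 | 0 | 1 − 0.95⁹ = 37.0% |
| 9 | 0.3 | 33% |
| 9 | 0.5 | 27% |
| 9 | 0.7 | 20% |
| 9 | 0.9 | 12% |

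Testing the visual analog scales after each segment, or measures at several visits, would add to this.

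**4. Two methods on DERS-16.** As a stand-in, the smaller p-value of a t test and a Mann-Whitney test was taken in 4,000 null data sets of 20 versus 20. This raised 5% to about 6.5%. The inflation on a single measure is small. The larger issue is that the reported effect depends on an unstated choice.

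**5. Price of keeping every measure primary.** With Bonferroni at d = 0.78, power falls from 0.67 to 0.56 for two components (.05/2) and to 0.33 for nine measures (.05/9).

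**6. Gain from baseline adjustment.** With correlation r between baseline and week 10, the effective effect is d/√(1 − r²). At r = 0.5 this is 0.78/√0.75 = 0.90, and power is 0.79. Across assumed r of 0.3, 0.5 and 0.7, power is 0.71, 0.79 and 0.92, against 0.67 unadjusted. The retest reliability of 0.88 cited for the DERS is not a baseline-to-week-10 correlation under treatment, so it is not used.

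**The case against.** The strongest reply is that carrying several candidate outcomes is deliberate. The trial puts feasibility first, wants to test whether psychophysiological measures are workable, and aims to identify the best measures for later use. Multiplicity rules and covariates may stand in an analysis plan that is not shown. This softens the consequence and is a good reason to keep every measure in the study. It does not settle which result is primary: the protocol itself labels a primary outcome, speaks of evaluating efficacy, and gives a confirmatory-style power statement for one unnamed comparison.

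Some stronger readings are tempting, but the documents do not support them:

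- *That a chance finding is likely.* The computed risk is about 10% to 37%, which is well above 5% but below one half. It also presumes a separate significance test on each measure, which the protocol does not announce.
- *That all nine measures face two competing tests.* The nonparametric and mixed-model text stands under the rating-scale heading, and the mixed model is assigned to DERS-16. The signals have their own section with regression models.
- *That there are firmly nine endpoints.* Objective Measures lists what is collected. Signal-specific processing is described only for skin conductance and heart rate, and the visual analog scales may be part of the reactivity component.
- *That the mixed model dilutes the effect by averaging over visits including baseline, or that effect sizes will come from raw post-treatment scores.* The text specifies neither. A condition-by-time contrast fits it equally well.
- *That bimonthly visits do not exist.* The written schedule has week 0, biweekly questionnaires, weeks 10-11 and week 22. However, the SPIRIT schedule in Figure 2 is not shown, and the word can mean twice a month.

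**Conclusion.** The point holds in a limited form. The protocol labels one primary outcome but supplies two unranked components that expand to as many as nine named measures (eight if accelerometry is only for artefact control). It gives no primary time point, no deciding analysis for DERS-16 and no baseline-adjusted effect size, while powering a single comparison at .05. If each measure is tested at .05, the false-positive chance is about 10% for the two components and roughly 12% to 37% for nine. The range rests on assumed correlations between 0.9 and 0. The proof-of-concept purpose lowers the stakes for any claim of efficacy. It raises them for the effect size carried forward, because supporting that power calculation is one of the trial's stated uses. This should be corrected; it does not undermine the design.

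**What to change.** - Name one primary efficacy contrast: the VR-CBT minus Calm Place difference in DERS-16 at week 10-11. Estimate it from the mixed model already planned, with baseline DERS-16 adjusted for (or constrained equal between groups) and with language, which the Translation section already promises to control.
- Report the standardised effect from that contrast with a 95% CI, and state that this is the estimate carried into the larger trial. If the data are non-normal, use a bootstrap or permutation interval in place of a second, competing test.
- Report reactivity metrics and visual analog scales as exploratory estimates with CIs. This keeps the aim of identifying suitable measures. DERS-16 is also the more practical choice because Objective Measures limits the repeat reactivity test to those completing 7 to 10 sessions, and no such limit is stated for the questionnaire.
- Reconcile 'bimonthly' with the visit schedule.

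The cost is a change of wording in the protocol and registry. No new data, visits or participants are needed. The downside is that reactivity loses co-primary status. In return, at d = 0.78 with 20 per group, power for the named contrast would rise from 0.67 to about 0.79 if the baseline-to-week-10 correlation were 0.5 (assumed).

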**Results:**

As this is the prospective registration of an RCT protocol, we do not yet report any results from the trial. Funding was confirmed in January 2020, and recruitment is expected to start in March 2023 and is set to finish in August 2025. The expected results are to be published in spring 2026.

**Conclusions:**

The proposed study responds to the community’s desire for accessible and appropriate resources for psychological well-being, as it was developed in active collaboration with the Inuit community in Québec. We will test feasibility and acceptance by comparing a culturally adapted, on-site psychotherapy with a commercial self-management program while incorporating novel technology and measurement in the area of Indigenous health. We also aim to fulfill the needs for RCT evidence of culturally adapted psychotherapies that are lacking in Canada.

**Trial Registration:**

International Standard Randomized Controlled Trial Number (ISRCTN) 21831510; https://www.isrctn.com/ISRCTN21831510

**International Registered Report Identifier (IRRID):**

PRR1-10.2196/40236

## Introduction

### Emotion Regulation and Mental Health

Emotion regulation is a set of skills and competencies that individuals have to a variable extent: strong emotion regulation skills can facilitate mental health. When those skills are dysregulated, the difficulties related to emotion regulation are implicated in various psychological complaints and disorders [1]. Biosignals such as heart rate, skin conductance, and diastolic blood pressure response are also phenotypical in populations with difficulties in emotion regulation, indicating multiple levels of involvement in the health of individuals [2]. Some psychotherapies exert to large effect, decreasing dysregulation and increasing the ability to regulate emotions [3-6]. Improvements in emotion regulation during psychotherapy are associated with decreases in anxiety, depression, substance use, and other psychopathologies [7]. Moreover, emotion regulation is robustly and longitudinally associated with psychological resilience [8] and associated with life satisfaction, positive affect, and other well-being indicators with a small to moderate effect size [9].

### Enhancing Emotion Regulation Interventions With Virtual Reality and Biofeedback

Virtual reality (VR)–assisted mental health interventions effectively increase mental well-being, including building the ability to regulate emotions [10-12]. VR is an interactive, computer-generated, 3D world of images, videos, and sounds delivered through a VR headset system. Combined with the efficacy of cognitive behavioral therapy (CBT), v*irtual reality–assisted cognitive behavioral therapy (VR-CBT)* has several therapeutic advantages, including increased interactivity of the therapy and patient participation. Immersive visuals can create a holistic approach to therapy with mind-body exercises (eg, biofeedback integrated with VR). Therapists can present clients with enhanced skill-building scenarios and modulate elements in the environment for the personal needs of the client. For instance, the varying intensity of the exposure can be shown to the client through visual aids that reflect their physiological states [13]. *Biofeedback* is a process of rapidly demonstrating physiological metrics to an individual, sometimes with the goal of changing thoughts, behaviors, or physiology [14].

### Integrating Inuit Culture, Community Needs, and Technology

In addition to therapeutic advantages, combining VR and CBT presents a unique opportunity for the advancement of cultural sensitivity in treatment. Up to 60% of Inuit live in urban centers, and many experience adversities in health [15]. Inuit residing in urban centers reported only fair or poor access to health care [16], and in Montreal, Indigenous peoples reported trauma, anxiety, and depression to be some of their primary concerns to be addressed [17]. The increased mental health risks and lack of culturally sensitive resources for First Nations, Métis, and Inuit are part of the complex consequences of ongoing settler colonialism. The mental health impacts of colonialism can be intergenerational, with adverse impacts documented into the second and possibly third generations [18,19]. The Indigenous historical and intergenerational trauma also stresses the importance of development and research with the aim of increasing the knowledge base toward strengthening resilience of the communities and their members.

Because of its relatively low cost, flexibility, and immersion, VR has been used in Indigenous contexts, such as in art, storytelling, culture, language, and transferring cultural heritage [20-23]. There is interest in digital technology solutions for Indigenous health and mental well-being; however, most follow a format of conventional psychotherapy via telemedicine [21,24]. VR could offer opportunities for access to mental health care resources for populations affected by health inequities, delivering specialized content at a low cost and in many locations.

### Co-design and Collaboration With Inuit in Québec

#### VR-CBT

To expand access to mental well-being resources for Inuit in Québec, we will evaluate the efficacy of 2 emotion regulation–based VR interventions in a proof-of-concept randomized controlled trial (RCT). Our team developed the VR-CBT with experts in psychotherapy, VR, and Inuit health and culture, including an Inuit advisory committee. The advisory committee was composed of Inuit and non-Inuit individuals, health and social services providers, and Inuit representational organizations. The advisory committee included both women and men. We consulted Inuit representational organizations before embarking on this project with the aim of naming research priorities and building a collaboration toward those goals. We then collaborated to culturally adapt the study procedures and materials. The process of culturally adapting the treatment manual and other materials will be described further in [name] et al, *in preparation*.

#### VR for Mental Well-Being: Self-management

Another application that is part of the study is Calm Place—a commercial VR program previously developed by Mimerse that involves guided relaxation and meditation techniques. The application has been used in clinical settings and is rooted in nature’s effects on well-being [25]. This intervention was chosen in consultation with the advisory committee based on the unacceptability of the waitlist or nonactive controls and similar therapeutic goals (eg, emotion regulation through guided activities).

### Research Aims

The primary aims of this proof-of-concept RCT are to investigate the feasibility, benefits, and challenges of a culturally adapted VR intervention versus an established VR self-management program. We will assess the feasibility and validity of psychophysiological measures as objective outcomes of the interventions. In addition, we estimate the effect size of each treatment through between-group and within-group measures of emotion regulation, mental well-being, and difficulties in mental well-being (anxiety, depression, and posttraumatic stress disorder) with a longitudinal follow-up.

We work in a novel area in the literature, providing a VR intervention for an Indigenous population with a specifically therapeutic aim [24]. In addition, we will use both objective and subjective outcome measures—a novel but robust approach [2]. This novel psychophysiological approach has been validated in healthy individuals in our laboratory ([name] et al, in preparation).

## Methods

### Design

The study design is a 2-arm proof-of-concept RCT co-designed with an Inuit advisory committee. The first treatment arm (A) is a 10-week VR-CBT. An active control treatment with minimal attention; the second treatment arm (B) will be using Calm Place as a 10-week self-management. There will be no crossover between conditions, and we will use a 1:1 ratio randomization procedure. The protocol is described in accordance with the SPIRIT (Standard Protocol Items: Recommendations for Interventional Trials) guidelines for interventional trials and is detailed in Multimedia Appendix 1. Ultimately, the goal of the study is to establish the initial feasibility of the VR-CBT and the technologies used and to identify the best measures for initial efficacy.

